**3.3.1 inclusion criteria**

- Patients have histologically or cytologically confirmed advanced or recurrent CRC;
- No prior systematic anti-cancer treatment and relapse or metastases was occurred more than 12 months after adjuvant chemotherapy;
- Patients have measurable disease as defined by RECIST 1.1 as determined by investigator;
- Patient with a history of radiotherapy at least 3 months before on the day of providing consent, but the measurable lesion should not be within the scope of radiotherapy;
- Patients with age of 18-75yr;
- Patients with a performance status of 0,1or 2 on the Eastern Cooperative Oncology Group.；
- Patients with Life expectancy of more than 12 weeks;
- Patients must have the ability to understand and sign the written informed consent voluntarily;
- Female of childbearing potential who are negative in a pregnancy test within 7 days before enrollment. Both male and female patients should agree to use an adequate method of contraception (total abstinence, an intrauterine device or hormone releasing system, a contraceptive implant and an oral contraceptive) starting with the first dose of study therapy through 120 days after the last dose of study therapy. Duration will be determined when the subject is assigned to treatment.

**Exclusion criteria**

- Patients with dMMR/MSI-H;
- Patients with major surgery or severe trauma within 4 weeks before the first medication;
- Patients with hypersensitivity to the components in the study protocol;；
- Patients who are ready to give birth or are pregnant;
- Patients with brain metastases who are unable to accurately describe the condition;
- Patients received immune-suppressive drugs 2 weeks before initial treatment (inhaled cortisol or other steroid hormones≤10 mg/day prednisone or equivalent pharmacophysiologic doses were excluded);
- Planned live attenuated vaccine within 4 weeks prior to or during study treatment;
- Patients have received anlotinib or anti-PD-1 monoclonal antibody therapy or other therapies that act on T-cell co-stimulation targets or checkpoints;
- Within 6 months prior to the start of study treatment, the following diseases appeared: myocardial infarction, severe/unstable angina, NYHA grade 2 or above congestive heart failure, poorly controlled arrhythmias, etc;
- Active hepatitis;
- Bone marrow, liver and kidney function did not meet the requirements of chemotherapy as follows:

- Neutrophil count<1,500/mm3;

- Platelet count <80,000/mm3;

- Total bilirubin >1.5-times the upper limit of normal;

-ALT/AST>2.5-times the upper limit of normal for patients without liver

metastases; (5.0-times the upper limit of normal for patients with

liver metastases)

- Creatinine >1.5-times the upper limit of normal;

- Patients with cancers other than advanced colorectal cancer within five years prior to the start of treatment in this study. Cervical carcinoma in situ, cured basal cell carcinoma and bladder epithelial tumor were excluded;
- History of substance abuse, drug use, alcohol dependence;
- Patients without legal capacity or limited civil capacity;
- Patients with autoimmune diseases or organ transplantation;
- Other situations that the investigator deemed inappropriate for enrollment;
  1. **Study Time**

According to about 1 patient per month, it takes about 20 months. The total study period is about 2-3 year.

- 1. **Withdrawn from the study**

Withdrawal cases refer to patients who stop taking drugs for various reasons in this trial. Patients with the following conditions will withdraw from the study:

• Patient or his legal representative requests to withdraw;

• According to the opinion of the researcher, it is harmful to the health of patients to continue to participate in the study;

• Patients with severe poor compliance or serious violation of the protocol;

• Pregnancy should be reported as a serious adverse event;

• Other diseases occurred in the course of the study. According to the judgment of the investigators, the disease will obviously affect the evaluation of the clinical situation of patients, and it is necessary to stop the treatment of this scheme;

• Patients develop a new malignant tumors that need treatment;

• Patients lost to follow-up;

• The use of prohibited drugs or other drugs that may lead to toxic reactions or bias the research results according to the judgment of researchers;

• The study drug treatment was suspended for more than 21 days;

• The patient died.

All patients who withdraw from the study should record the reason for withdrawal in the case report form and the patient's medical record.

All patients who withdraw due to adverse events or laboratory abnormalities should be followed up until the adverse events recover or stabilize, and the subsequent results of the events should be recorded. If any patient died during the trial or within 30 days after completion of the trial, the investigator should be informed. The cause of death must be recorded in detail on the serious adverse event (SAE) report form within 24 hours.

- 1. **Procedures**

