| Duration of study participation | The investigational drug will be repeatedly administered until the criteria for discontinuation are met. In the event that the treatment is discontinued for reasons other than an exacerbation of the underlying disease via imaging (e.g., unacceptable side effects), tumor evaluation follow-up will continue until either an exacerbation of the underlying disease is observed via imaging or a new anticancer treatment is initiated, whichever happens first. |
| Administration method | Eligible patients were given sintilimab intravenously at a dose of 200mg on day 1, and anlotinib orally at a dosage of 12mg daily from days 1-14 every 3 weeks. Treatment was maintained until progressive disease (PD), treatment intolerance, death, or withdrawal of consent, with one cycle as 3 weeks. |
| Safety evaluation | Evaluations will be performed using CTCAE version 5.0. |
| Efficacy evaluation | The efficacy will be evaluated in accordance with RECIST version 1.1 every 6 weeks.  ・Image evaluation: computed tomography (CT) or magnetic resonance imaging (MRI) |
| Observations and tests | Physical examination, vital signs, PS, laboratory tests (hematology and biochemistry), urinalysis, tumor markers, ECG, CT of chest, abdomen, and pelvis, etc. |
| Trial Design | APICAL-CRC trial was an investigator-initiated, open-label, non-randomized, single-arm, phase II clinical trial using Simon’s minimax two-stage design. The combination of anlotinib plus sintilimab is expected to result in an improved ORR of 35%. The null hypothesis, which stated that the true ORR was 15%, would be tested against a one-sided alternative of 35%, with 80% power and a type I error rate of 5%. In the first stage, the study accrued 15 patients. If less than two response or no response was observed, the study was terminated and deemed negative. Otherwise, an additional 13 patients would be accrued for the second stage. The study was considered positive if there were more than 9 responders among the 28 patients. |

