**3.6.2 Dose delay and dose adjustment of medication**

The toxicity of patients should be carefully monitored, and the dose should be adjusted according to the severity of adverse effect. It is suggested that the dose should be adjusted according to the most serious toxic reactions and laboratory abnormalities in the previous course of treatment or this course of treatment. The level of toxicity should be in accordance with NCI-CTCAE 5.0. If there are multiple toxic reactions, the dose should be adjusted according to the most serious toxic reaction.

The longest time allowed for treatment delay is 3 weeks, during which the symptoms should be relieved to CTCAE grade 1 or below. For patients with CTCAE grade 2 or more severe toxicity at baseline, symptoms should be reduced to baseline level.

Medication can be reduced / discontinued due to adverse events at any stage of the study.

If patients need to suspend treatment for more than 3 weeks due to treatment-related adverse reactions/toxicity, and the symptoms cannot be controlled even after the best supportive treatment, they should withdraw from the study.

If patients need to be hospitalized due to treatment-related adverse reactions / toxicities during the chemotherapy phase, all study drugs should be discontinued before all symptoms recover.

All adverse events should be graded according to NCI-CTCAE version 5.0.

If patients need to reduce anlotinib more than two times due to toxicity, they should withdraw from the study.

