**3.6.2.1 dose adjustment of medication**

The management of toxicity involved supportive care, as well as prescheduled reduction in the dose of anlotinib, and interruptions of anlotnib dose until adverse events were tolerable (grade 2 or lower). Anlotinib could be reduced if patients had intolerable grade 2 or grade 3 treatment-related adverse events, which were judged by the investigators. The first dose-reduction of anlotinib was 10mg daily, the second dose-reduction of anlotinib was 8mg daily. If patients still could not tolerate to 8mg daily, anlotinib would be terminated. If anlotinib dose was reduced or interrupted, the dose could not be increases during subsequent cycles. Modifications to the sintilimab dose were not permitted. Patients who had intolerable adverse events (AEs) leading to the delay or cessation of one medication continued treatment with the other.

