**3.7.4.1 Treatment period**

- The screening phase should be conducted within 28 days before the start of study drug treatment.
- Treatment period refers to the interval from the use of the first drug treatment to the withdrawal of the patient from the study drug treatment.
- Patients will enter the post-treatment follow-up period after discontinuing the study drug treatment. This period should include contacting the patient every 3 months until 1 year after progression or recording the patient's death to collect the data of overall survival.

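### Section 3.5 treats stopping study drug as leaving the study, which contradicts the rules that keep these patients in tumour and survival follow-up

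*Protocol*

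**What the plan says.** Section 3.5 of the protocol (Withdrawn from the study) opens: "Withdrawal cases refer to patients who stop taking drugs for various reasons in this trial. Patients with the following conditions will withdraw from the study". The list that follows contains two kinds of event:

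- Events that end treatment: "The study drug treatment was suspended for more than 21 days"; an intercurrent condition ("Other diseases occurred in the course of the study") judged to require stopping; a new malignancy; prohibited drugs; poor compliance.
- Events that can end observation: the patient's request, loss to follow-up, death.

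Progression is not listed. The follow-up that 3.5 itself provides is: "All patients who withdraw due to adverse events or laboratory abnormalities should be followed up until the adverse events recover or stabilize". It does not mention scans or survival contact and does not refer to any other section.

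Elsewhere the protocol keeps the same patients under observation. For treatment stopped for reasons other than imaging progression, the synopsis (Duration of study participation) reads "unacceptable side effects), tumor evaluation follow-up will continue until either an exacerbation of the underlying disease is observed via imaging", or until new anticancer treatment starts if that comes first. Section 3.7.4.1 says: "Patients will enter the post-treatment follow-up period after discontinuing the study drug treatment", with survival contact every 3 months. Section 3.8.3 has patients who end without progression examined every 3 months until they progress.

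**The concern.** A patient whose drug is held for more than 21 days because of toxicity is out of the study under 3.5, but still due for scans and survival calls under the synopsis and 3.7.4.1. Both instructions cannot be followed.

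If 3.5 were followed to the letter, PFS and OS observation would end at toxicity, intercurrent illness or poor compliance, any of which may be related to prognosis. The protocol estimates both endpoints by Kaplan-Meier, which assumes that censoring carries no information about later risk. A statistical analysis plan can set censoring rules, but it cannot recover scans and contacts that were never made, so the question of who stays under observation belongs in the protocol.

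There is a smaller effect on response. Section 5.1.1 removes patients with no post-baseline efficacy assessment from the efficacy-evaluable set, one of the two sets in which ORR is reported. A patient who leaves before the first 6-week scan falls into that group. With 28 patients planned, each one is 1/28 = 3.6 percentage points.

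**Working it through.** **Passages side by side: a patient who stops for toxicity without progression**

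| Place | Status after the stop |
| --- | --- |
| 3.5 | Withdrawn from the study; followed until the adverse event resolves or stabilises |
| 3.6.2 | Two toxicity rules also worded as leaving the study, one of them "If patients need to reduce anlotinib more than two times due to toxicity, they should withdraw from the study" |
| 3.6.2.1 | "Patients who had intolerable adverse events (AEs) leading to the delay or cessation of one medication continued treatment with the other" |
| 3.6.2.3, Table 1 | No recovery after a 21-day delay: treatment is withdrawn; leaving the study is not mentioned |
| Synopsis | Tumour evaluation continues to imaging progression or new anticancer treatment |
| 3.7.4.1 | Enters post-treatment follow-up with 3-monthly survival contact |
| 3.8.3 | Examined every 3 months until progression |
| Flow-chart | After-treatment CT every 8 weeks until progression |

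The first two rows conflict with the rest. The last two also differ from each other on the interval.

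**Illustration of size**

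The protocol gives no figure on this point, so there is none to reproduce. Inputs:

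- Median PFS while on drug: 6.3 months, used only for scale. Section 1.3 quotes it for an earlier regorafenib plus nivolumab study in colorectal cancer. λ = ln 2 / 6.3 = 0.110 per month.
- Share *q* stopping drug before progression: 10%, 20%, 30% (assumed). Stop hazard μ = λq/(1 − q), which gives 0.0122, 0.0275 and 0.0472 per month.
- Progression hazard after the stop: kλ, with k = 1, 1.5, 2, 3 (assumed).

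If patients are censored at the stop, Kaplan-Meier recovers only the on-drug hazard λ, so the median is 6.3 months. With follow-up kept to progression, and d = λ + μ − kλ,

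S(t) = exp(−(λ+μ)t) + μ·exp(−kλt)·(1 − exp(−dt))/d.

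Setting S(t) = 0.5 gives the median under full follow-up. The overstatement is 6.3 divided by that median, minus 1.

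| q | k = 1 | k = 1.5 | k = 2 | k = 3 |
| --- | --- | --- | --- | --- |
| 10% | 6.30 (0%) | 6.20 (1.7%) | 6.12 (3.0%) | 6.01 (4.9%) |
| 20% | 6.30 (0%) | 6.08 (3.6%) | 5.92 (6.4%) | 5.70 (10.5%) |
| 30% | 6.30 (0%) | 5.95 (5.9%) | 5.71 (10.4%) | 5.38 (17.0%) |

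Check at q = 30%, k = 3, t = 5.38: d = 0.1100 + 0.0472 − 0.3301 = −0.173. The two terms are 0.429 and 0.071, which sum to 0.500.

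The percentages do not depend on the 6.3 months, because λ only sets the time scale. Below k = 1 the sign changes: at k = 0.75 and q = 20% the full-follow-up median is 6.44 months, so censoring at the stop understates it by 2.2%.

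**The case against.** The best defence is that the protocol uses its terms loosely and that end of treatment is meant. A flow-chart note speaks of withdrawing from the study because of progression, yet the same table has an after-progression column for survival. Section 3.8.3 says end of study and then continues examinations. Read literally, the first sentence of 3.5 would also cover patients who stop for progression, and section 3.8.5 follows those for survival. The adverse-event sentence in 3.5 can be read as a safety rule that leaves other follow-up untouched. The trial has a single centre, so sites cannot diverge. All of this makes the benign reading the likelier one. It does not remove the contradiction: staff who consult 3.5 alone are told that the patient has left, and nothing there points them to the other sections.

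A reader might infer more than the text supports:

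- *That PFS and OS will be censored at drug stop.* No passage ends scans or survival contacts, and the protocol states no censoring rule. The consequence is conditional on a literal application of 3.5.
- *That the medians are biased upward.* That needs a higher hazard after the stop, and the documents give no figure for it.
- *That a size can be given for OS, or a number of lost PFS events.* The PFS model does not carry over to OS, because stops without progression can occur only while the patient is on drug, and treatment ends at progression. A count of lost events would assume that every patient progresses under observation.
- *That the primary result is compromised.* A patient without a scan leaves only the efficacy-evaluable set and stays in ITT.

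**Conclusion.** The contradiction stands on the text and should be corrected. It is a wording conflict that puts PFS and OS observation at risk; it is no evidence that follow-up will be lost. If 3.5 were applied literally, the Kaplan-Meier median PFS would be overstated by 0% to 17%, given constant hazards, 10% to 30% stopping without progression and a hazard 1 to 3 times as high after the stop. It would be understated if the hazard fell. None of these inputs comes from the documents. The exposure is mainly to secondary, descriptive endpoints. ORR is touched only through patients who stop before the first scan, and only in the efficacy-evaluable set.

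**What to change.** Split section 3.5 in two.

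1. *Discontinuation of study treatment.* Keep the existing list of conditions, with a lead-in such as: 'Study treatment is discontinued in patients with the following conditions.'
2. *End of study participation.* Limit this to withdrawal of consent to follow-up, loss to follow-up and death. A request to stop drug should be recorded separately from a request to stop follow-up.

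Then add: 'Patients who discontinue study treatment continue tumour assessment and survival follow-up as described in the synopsis and sections 3.7.4.1 and 3.8.3, and remain in the ITT analysis.'

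The sponsor should also reconcile two related conflicts; which clinical rule or schedule applies is for the sponsor to decide:

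- the study-withdrawal wording in 3.6.2 against 3.6.2.1 and Table 1 in 3.6.2.3, which stop one drug or the treatment;
- the post-treatment assessment interval, 3-monthly in 3.8.3 and 8-weekly in the flow-chart.

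The cost is a wording amendment. The scans and contacts are already required by the synopsis, 3.7.4.1 and 3.8.3.

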**3.6.1 The use of Medication**

Eligible patients were given sintilimab intravenously at a dose of 200mg on day 1, and anlotinib orally at a dosage of 12mg daily from days 1-14 every 3 weeks. Treatment was maintained until progressive disease (PD), treatment intolerance, death, development of intolerable toxicity, or withdrawal of consent, with one cycle as 3 weeks.

**3.6.2 Dose delay and dose adjustment of medication**

The toxicity of patients should be carefully monitored, and the dose should be adjusted according to the severity of adverse effect. It is suggested that the dose should be adjusted according to the most serious toxic reactions and laboratory abnormalities in the previous course of treatment or this course of treatment. The level of toxicity should be in accordance with NCI-CTCAE 5.0. If there are multiple toxic reactions, the dose should be adjusted according to the most serious toxic reaction.

The longest time allowed for treatment delay is 3 weeks, during which the symptoms should be relieved to CTCAE grade 1 or below. For patients with CTCAE grade 2 or more severe toxicity at baseline, symptoms should be reduced to baseline level.

Medication can be reduced / discontinued due to adverse events at any stage of the study.

If patients need to suspend treatment for more than 3 weeks due to treatment-related adverse reactions/toxicity, and the symptoms cannot be controlled even after the best supportive treatment, they should withdraw from the study.

If patients need to be hospitalized due to treatment-related adverse reactions / toxicities during the chemotherapy phase, all study drugs should be discontinued before all symptoms recover.

All adverse events should be graded according to NCI-CTCAE version 5.0.

If patients need to reduce anlotinib more than two times due to toxicity, they should withdraw from the study.

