**3.6.2.2 The necessary laboratory test results at the beginning of the next cycle of chemotherapy,**

- - - ANC count ≥1.5×109/L,
    - Platelet count≥80×10^9^/L,
    - Serum creatinine <1.5×ULN,
    - Serum total bilirubin≤1.5-times the upper limit of normal for patients without liver metastases; (3.0-times the upper limit of normal for patients without liver metastases)；,
    - AST/ALT ≤2.5-times the upper limit of normal for patients without liver metastases; (5.0-times the upper limit of normal for patients without liver metastases)

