**3.6.3 Concomitant treatment**

**3.6.3.1** **Unallowed Treatment**

• Except for Anlotinib plus Sintilimab, no other anticancer drugs are allowed,

• Research drugs (e.g. research antibiotics, antiemetics, etc.).

• In the course of treatment, any Chinese herbal medicine treatment with anti-tumor as the indication.

• Radiotherapy, except palliative radiotherapy for existing bone metastases.

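### For a patient admitted with a treatment-related toxicity that delays or stops one drug, sections 3.6.2 and 3.6.2.1 give opposite instructions for the other drug, and neither is said to take precedence

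*Protocol*

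**What the plan says.** The regimen in section 3.6.1 has two drugs: "sintilimab intravenously at a dose of 200mg on day 1, and anlotinib orally at a dosage of 12mg daily from days 1-14 every 3 weeks". Section 3.6.3.1 rules out anything further against the tumour: "Except for Anlotinib plus Sintilimab, no other anticancer drugs are allowed".

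Three places govern what happens to these drugs when toxicity occurs.

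- **Section 3.6.2** has a hospitalisation rule. Its trigger is admission for treatment-related toxicity, and its limit and action read "during the chemotherapy phase, all study drugs should be discontinued before all symptoms recover". The sensible reading of the action is that both drugs are held until symptoms have resolved.
- **Section 3.6.2.1** has a one-drug rule. Patients with intolerable adverse events "leading to the delay or cessation of one medication continued treatment with the other". Hospitalisation is not mentioned.
- **Table 1 (section 3.6.2.3)** sets grade 3-4 actions separately by drug. Anlotinib is stopped and then reduced. The sintilimab dose is not modified, but the drug may be stopped or re-challenged under immune-event instructions. Hospitalisation is not mentioned here either.

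For the time on study drug, section 3.7.4.1 supplies a defined term: "Treatment period refers to the interval from the use of the first drug treatment" up to withdrawal from study drug. No chemotherapy phase is defined there or among the trial phases in section 3.8.

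**The concern.** Two rules can be triggered by the same event. One stops everything, the other keeps one drug going, and nothing says which governs. The hold in 3.6.2 concerns toxicity severe enough for admission, which under section 6.2.2 will usually be a serious adverse event. An ambiguity here therefore bears on how patients with serious events are treated.

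Two investigators following the text in good faith could give the same inpatient different treatment. That would make exposure, and the safety profile read against it, depend on which section was consulted. It may also affect when a patient meets the withdrawal criterion in section 3.5 for suspending study treatment beyond 21 days, because that criterion does not say whether holding only one of the two drugs counts.

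The wording of the trigger adds to the doubt, since it limits the hold to a phase that the protocol does not define.

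**Working it through.** No sample size, power or error rate enters this point, and the protocol gives no figure to reproduce. The check is a comparison of text.

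**Step 1: triggers and actions side by side.**

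| Place | Trigger | Action |
| --- | --- | --- |
| 3.6.2 | Admission for treatment-related toxicity | All study drugs held |
| 3.6.2.1 | Intolerable adverse event that delays or stops one drug | The other drug continues |
| Table 1 | Grade 3-4 treatment-related toxicity | Anlotinib held and reduced; sintilimab handled on its own terms |

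**Step 2: which patients meet both of the first two triggers.**

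- (a) Admitted, and the toxicity leads to delay or cessation of one drug: both rules apply. For example, if anlotinib is the drug stopped, 3.6.2 withholds sintilimab and 3.6.2.1 continues it. The instructions are opposite.
- (b) Admitted, and the toxicity leads to both drugs being stopped: 3.6.2.1 has no other drug to continue, so there is no conflict.
- (c) Not admitted: the hospitalisation rule is not triggered, so there is no conflict.

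The conflict is confined to case (a).

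**Step 3: is precedence stated?** Section 3.6.2.1 has no inpatient exception and no reference back to the hospitalisation rule. Section 3.6.2 does not say that it overrides the one-drug rule. Table 1 is silent. Precedence is therefore not stated.

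**Step 4: what the chemotherapy phase can mean.** The regimen contains no chemotherapy. However, the protocol uses the word for study treatment elsewhere: the heading of section 3.6.2.2 reads "The necessary laboratory test results at the beginning of the next cycle of chemotherapy", and note 4 to the study flow chart uses it in the same way. Section 3.6.3.2 still carries an instruction about irinotecan, which is not a study drug, so text from another regimen has survived. The phrase most plausibly stands for the treatment period. On that reading the hold is live and case (a) arises.

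**The case against.** The strongest reply is that the rules sit at different levels. The hospitalisation rule is specific and strict; the one-drug rule is general. Once admission stops all drugs, the patient is no longer someone with one drug stopped, so 3.6.2.1 is not reached. On this reading the two sections are compatible. Table 1 adds no contradiction of its own: it is organised by grade, and its sintilimab entry permits stopping.

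This reading is possible, but the text does not compel it. The hospitalisation sentence carries leftover wording, while 3.6.2.1 and Table 1 are written for this regimen and treat the drugs separately. A similar tension appears where admission plays no part. Section 3.6.2 withdraws a patient who needs more than two anlotinib reductions, whereas 3.6.2.1 ends anlotinib when the second reduced dose is not tolerated and lets the other drug continue. That looks more like two unreconciled sets of rules than a deliberate hierarchy.

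Some of the reply stands. Section 3.6.2.1 never says that a hospitalised patient continues the other drug, and a fair description of the defect is overlap without stated precedence.

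A reader might also infer that the hold never applies because no chemotherapy phase exists. The document does not support that: it uses the word loosely for study treatment, and the sentence itself orders all study drugs to be held.

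**Conclusion.** The point holds for hospitalised patients whose treatment-related toxicity leads to delay or cessation of one drug. For them the protocol gives opposite instructions for the other drug and no order of precedence. Separately, the hold is tied to an undefined phase. This rests on reading that phase as the treatment period and on the absence of any linking sentence among 3.6.2, 3.6.2.1 and Table 1.

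Two stronger conclusions are tempting and are not supported.

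- *Every patient hospitalised for toxicity is affected.* Case (b) shows otherwise. The protocol gives no admission rate. Assumed rates of 10%, 20% or 30% of 28 patients would give 28 × 0.10 = 2.8, 28 × 0.20 = 5.6 or 28 × 0.30 = 8.4 admissions, but these count all such admissions. They are only upper bounds on conflicting cases at rates that nothing in the document supports.
- *The primary response rate is biased.* Any effect runs indirectly through exposure and withdrawal, and neither its direction nor its size can be derived from the document.

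The matter still deserves correction, because it concerns patients with serious toxicity and the correction is cheap.

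**What to change.** Reconcile section 3.6.2, section 3.6.2.1 and Table 1 so that a single rule states which drug or drugs are held when a treatment-related event needs hospitalisation, and whether the instruction to continue the other drug applies to those patients. Put a cross-reference in each of the three places. Replace the chemotherapy phase with the treatment period defined in section 3.7.4.1. Which clinical rule is right is for the investigator to decide; this review takes no position on it.

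The cost is amendment wording, with no extra patients, visits or procedures.

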**3.6.2.3 Dose adjustment** **plan for next cycle**

| Table 1: Dose adjustment for treatment-related toxicity | |
| --- | --- |
|  | Grade 3-4 adverse events |
| Anlotinib | The drug was stopped until the toxicity was reduced to Grade 2, and then the dose was reduced to 10mg qd at first dose-reduction, further 8mg qd at second dose-reduction. If not tolerate to 8mg qd, then anlotinib was terminated. |
| Sintilimab | Modifications to the sintilimab dose were not permitted. Sintilimab could be stopped or re-challenged according to the instruction of immune-AE. |
| If the patient cannot recover after 21 days delay, the treatment should be withdrawn. According to NCI-CTCAE 5.0 | |

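### A patient who cannot tolerate anlotinib 8 mg must leave the study under Protocol 3.6.2, but under 3.6.2.1 stops anlotinib only and stays on sintilimab

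*Protocol*

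**What the plan says.** Protocol 3.6.2, the general section on delays and dose changes, states: "If patients need to reduce anlotinib more than two times due to toxicity, they should withdraw from the study". Section 3.5 explains what withdrawal means: "Withdrawal cases refer to patients who stop taking drugs for various reasons in this trial".

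Section 3.6.2.1 sets the anlotinib steps (10 mg at the first reduction, 8 mg at the second) and then says: "If patients still could not tolerate to 8mg daily, anlotinib would be terminated". It adds: "Patients who had intolerable adverse events (AEs) leading to the delay or cessation of one medication continued treatment with the other". Table 1 in 3.6.2.3 repeats the stop: "If not tolerate to 8mg qd, then anlotinib was terminated". Its sintilimab row forbids dose changes and refers stopping or rechallenge to immune-event guidance. It does not say what happens to sintilimab once anlotinib has ended.

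On recovery from toxicity, 3.6.2 caps a treatment delay at 3 weeks, "during which the symptoms should be relieved to CTCAE grade 1 or below", with an exception: "For patients with CTCAE grade 2 or more severe toxicity at baseline, symptoms should be reduced to baseline level". Section 3.6.2.1 provides for "interruptions of anlotnib dose until adverse events were tolerable (grade 2 or lower"), and Table 1 holds anlotinib until grade 2 and then gives the reduced dose.

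**The concern.** Dose modification and withdrawal are protocol rules, and an investigator has to apply them at the bedside. When 8 mg fails, the section consulted decides whether the patient goes on receiving sintilimab or stops all study treatment. It also decides who is recorded as withdrawn, with a reason, in the case report form. Because each instruction breaches the other, a protocol deviation cannot be judged consistently for these patients. What is at stake is safety management, drug exposure and equal handling of patients.

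**Working it through.** No stated figure has to be reproduced. The check is to apply each rule to the same patient.

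**Step 1: identify the patient.** Inputs: starting dose 12 mg on days 1 to 14 of a 21-day cycle (3.6.1); reductions to 10 mg and 8 mg (3.6.2.1, Table 1).

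| Step | Daily dose | Per cycle | Share of full dose |
|---|---|---|---|
| Start | 12 mg | 12 × 14 = 168 mg | 100% |
| First reduction | 10 mg | 10 × 14 = 140 mg | 140/168 = 83% |
| Second reduction | 8 mg | 8 × 14 = 112 mg | 112/168 = 67% |

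There is no step below 8 mg. Needing more than two reductions and failing to tolerate 8 mg are therefore the same condition.

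**Step 2: apply each rule to that patient.**

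| Source | Anlotinib | Sintilimab per cycle | On study? |
|---|---|---|---|
| 3.6.2, with 3.5 | 0 mg | 0 mg | Withdrawn |
| 3.6.2.1 | 0 mg | 200 mg | Still treated |
| Table 1 | 0 mg | Not stated | Not stated |

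**Step 3: look for a reading that reconciles them.**
- Withdrawal cannot mean stopping anlotinib alone. The 3.6.2 sentence concerns the study, and 3.5 describes withdrawn patients as having stopped taking drugs. A patient cannot do that and continue sintilimab.
- Letting the specific rule override the general one does not help. The 3.6.2 sentence is itself about anlotinib reductions and has the same trigger.
- The protocol contains no precedence clause.

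**Step 4: check the 21-day rule.** Section 3.5 also withdraws patients whose study drug treatment is suspended for more than 21 days. Once anlotinib ends for good, the patient will be off it for longer than that. Unless the limit applies only when both drugs are held, it could remove a patient whom 3.6.2.1 keeps on sintilimab.

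**Step 5: recovery grade.** Take a first grade 3 event that settles at grade 2, in a patient without that toxicity at baseline. Table 1 allows 140 mg in the next cycle at once. If 3.6.2 is the restart rule, the patient waits up to 3 weeks for grade 1 and then receives the same reduced dose. The difference is timing, plus possible discontinuation if grade 1 is not reached within the limit. For a patient with grade 2 toxicity at baseline, 3.6.2 asks only for a return to baseline, so the rules largely agree.

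**Step 6: nearby slips.** In 3.6.2.2 the limits for bilirubin (1.5 and 3.0 times the upper limit of normal) and for AST/ALT (2.5 and 5.0 times) are both assigned to patients without liver metastases. That group has two limits for each test and the other group has none. The exclusion criteria assign the 5.0-fold ALT/AST limit to patients with liver metastases. Section 3.6.3.2 suspends irinotecan during radiotherapy, which is not a study drug.

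**The case against.** The best defence is that most of the text points one way. Both 3.6.2.1 and Table 1 end anlotinib only. The withdrawal list in 3.5 has no entry for repeated anlotinib reductions, although it does list suspension beyond 21 days. The 3.6.2 sentence sits in a section that also speaks of a chemotherapy phase, in a regimen without chemotherapy, and so may be leftover text. The trial is single-centre, so sites cannot diverge. Tumour assessment continues, according to the synopsis, when treatment stops for reasons other than progression on imaging.

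This makes it likely which rule was meant and limits the consequences. It does not remove the instruction to withdraw, which is still in force as written.

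On recovery grade the defence goes further. Section 3.6.2 speaks of treatment delay in general, while 3.6.2.1 and Table 1 speak of anlotinib, so a general and a drug-specific rule may both be intended. A reader might infer a second contradiction, worth 140 mg against 0 mg of anlotinib. The protocol does not support that, because 3.6.2 allows up to 3 weeks for recovery and the reduced dose can follow. This is an ambiguity to clarify.

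**Conclusion.** The 8 mg conflict is real and should be fixed. Section 3.6.2 withdraws the patient and 3.6.2.1 continues sintilimab. Table 1 supports stopping anlotinib and is silent on the rest. For each affected patient the size is sintilimab 200 mg per 21-day cycle or none. The protocol does not say how many of the 28 planned patients might be affected, and no number is assumed here. The conclusion rests on there being no anlotinib step below 8 mg, which 3.6.2.1 and Table 1 both support.

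Two stronger readings should be resisted. A reader might infer that the primary result is at risk. The documents do not support this: sample size, error rates and the ITT analysis of objective response do not depend on which rule is kept. A reader might also infer that Table 1 itself continues sintilimab after anlotinib ends, but it does not say so.

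The recovery grade is a secondary point for clarification. The slips in 3.6.2.2 and 3.6.3.2 are separate and add no weight to the main point, although the laboratory limits cannot be applied as written.

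**What to change.** 1. In 3.6.2, replace the withdrawal sentence with: *If anlotinib 8 mg daily is not tolerated, anlotinib is terminated and sintilimab is continued per 3.6.2.1; the patient remains on study.* Add the same statement to Table 1.
2. In 3.5, state that the 21-day suspension rule applies when both drugs are suspended, and word the 21-day line under Table 1 to match.
3. If the sponsor intends withdrawal instead, keep 3.6.2 and change 3.6.2.1 and Table 1 to say so.
4. State whether grade 1 (or baseline) in 3.6.2, or grade 2 in 3.6.2.1 and Table 1, governs an anlotinib restart.
5. In 3.6.2.2, assign the bracketed bilirubin and AST/ALT limits to patients with liver metastases. In 3.6.3.2, replace irinotecan with the study drug to be held.

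The cost is amendment wording and notice to the site. No extra patients, procedures or analyses are needed.
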